### Inclusion criteria

Patients older than 18 years with confirmed diagnosis of COVID-19 according to guidelines given by the World Health Organization and according to each institutional and/or local guideline, andwho requires in-hospital management for more than 24 hours related to COVID-19, orwho dies during the first 24 hours after hospital admission

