### Study design

The CARDIO COVID 19-20 Registry is an observational, multicenter, ambispective, and hospital-based registry that includes patients with confirmed COVID-19 that require in-hospital treatment in Latin American medical institutions. Enrollment of patients started on May 01, 2020 and was initially planned to last three months; however, based on the progression of the pandemic in Latin America, enrollment was extended until December 2020, and could be extended once again based on the pandemic course in this continent at that time.

The Scientific Committee is composed by members of the Council of Heart Failure and Pulmonary Hypertension (CIFACAH) and the Interamerican Society of Cardiology (IASC). It has the approval of the Clinical Research Center (CIC) and the Ethics Committee of the Fundación Valle del Lili (FVL) and the Scientific and Academic approval of IASC.

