### Site selection

The Steering Committee of the Registry designated a national coordinator in the 20 Latin American countries that will be included; from Central America: Mexico, Guatemala, Honduras, El Salvador, Nicaragua, Costa Rica, Panama, Dominican Republic, Cuba and Puerto Rico; and from South America: Colombia, Venezuela, Brazil, Ecuador, Peru, Bolivia, Uruguay, Paraguay, Chile and Argentina. (Figure 1) The IASC and CIFACAH are working with those designated national coordinators and the presidents of the national cardiovascular societies or associations of these countries (who must be affiliated to the IASC) to identify potential researchers (e.g., internal medicine specialists, cardiologists or intensivists) that will be contacted and invited to participate in this project. Those identified professionals and institutions must complete a digital form submitting data to the research team (principal investigator and sub investigator).

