COPD: Chronic Obstructive Pulmonary Disease; ARB: Angiotensin-Receptor Blockers; ACEi: Angiotensin-Converting Enzyme Inhibitors; ARNI: Angiotensin Receptor Neprilysin Inhibitor; RV: Right Ventricle; LV: Left Ventricle; IABP: Intra-Aortic Balloon Pump; ECMO: Extracorporeal Membrane Oxygenation.

Each institution will be coded, as well as the identity of every enrolled patient. Weekly quality control will be carried out in each participant center in order to verify the integrity of the data collected and will be informed about discrepancies found in the registered data.

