## Data Analysis

This study will obtain different data that will be used to calculate lethality and frequency of complications during hospitalization and follow-up, and to characterize the overall in-hospital population. Hospital fatality (number of deaths attributed by COVID-19/number of patients diagnosed with COVID-19), incidence of in-hospital cardiovascular complications (number of new complications due to specific cardiovascular cause in COVID-19 patients/number of patients diagnosed with COVID-19), and survival analysis (the probability of death by time interval can be calculated) will be determined by the Kaplan Meier method and presented by a graph.

Characterization of the in-hospital population will be carried out through an univariate analysis to determine the behavior of numerical variables, the normality of the variables will be determined with a Shapiro Wilk test, those with a p > 0.05 will be considered with normal distribution and will be presented with averages and standard deviation; those with a non-normal distribution will be presented with median and interquartile ranges. The categorical variables will be presented as proportions.

The quantitative variables will be compared, in case of a normal distribution, by the Student’s t-test or ANOVA. If the normality criterion is not met, a non-parametric test will be used. For the comparison of categorical variables, Fisher’s exact test or X^2^ test will be used. For the analysis of patient outcomes with COVID-19 based on demographic, laboratory values, and/or clinical variables, the relation of these variables will be evaluated with a multivariate logistic or linear regression models, depending on the outcome variable to evaluate.

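### The named tests and regression models leave out hospital, country and admission period, so risk-factor associations can be confounded by site and pandemic period, and uncertainty is understated for factors that vary between sites

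*Protocol article*

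**What the plan says.** The Study design section describes an "observational, multicenter, ambispective, and hospital-based registry that includes patients with confirmed COVID-19". Under Site selection, the Steering Committee "designated a national coordinator in the 20 Latin American countries that will be included". Diagnosis follows World Health Organization guidance and is also made "according to each institutional and/or local guideline" (Inclusion criteria), so the way a case is confirmed may differ between hospitals. On timing, "Enrollment of patients started on May 01, 2020 and was initially planned to last three months"; later "enrollment was extended until December 2020, and could be extended once again based on the pandemic course". From 1 May until December 2020 is about seven to eight months.

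The Data Analysis section names Student's t-test or ANOVA, an unspecified non-parametric alternative, Fisher's exact or chi-square tests, and Kaplan-Meier. For outcomes, "the relation of these variables will be evaluated with a multivariate logistic or linear regression models". The explanatory variables are given by class: demographic, laboratory and clinical. Hospital, country and admission period are not among them, and no random effect, generalised estimating equation, stratification or robust variance is named. The site identifier does exist: "Each institution will be coded, as well as the identity of every enrolled patient" (Data Collection).

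**The concern.** In their standard form all the named methods treat patients as independent. Patients in one hospital share a local case definition and local practice, and those admitted in the same months share a stage of the pandemic. Two separate problems follow.

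- **Confounding.** If hospitals or months with more of some comorbidity also have higher mortality for other reasons, a model without centre and period assigns that difference to the comorbidity. The coefficient itself is then wrong, and more patients do not cure it.
- **Precision.** If outcomes are correlated within hospitals, the usual standard error is too small for any quantity that carries between-hospital variation. That covers factors whose frequency differs by site, and intervals on overall fatality or complication rates.

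The abstract's conclusion makes identification of risk factors the purpose of the registry, so the exposed analyses are its main inferential product.

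**Working it through.** The article states no number of hospitals, patients per hospital, ICC, sample size or alpha, so there is no planned figure to reproduce. All inputs below are assumptions, shown over a range.

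**Step 1. Intervals on overall rates, and site-level factors.** The design effect is DEFF = 1 + (m − 1) × ICC, where m is patients per site and the ICC is on the observed scale. The correct interval is √DEFF times as wide as the independence interval. A nominal two-sided 5% test has actual size 2 × (1 − Φ(1.96/√DEFF)). For example, m = 50 and ICC = 0.05 give DEFF = 1 + 49 × 0.05 = 3.45 and √3.45 = 1.86.

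| m | ICC | DEFF | Width factor | Actual size |
|---|---|---|---|---|
| 20 | 0.01 | 1.19 | 1.09 | 0.072 |
| 20 | 0.05 | 1.95 | 1.40 | 0.160 |
| 20 | 0.10 | 2.90 | 1.70 | 0.250 |
| 50 | 0.01 | 1.49 | 1.22 | 0.108 |
| 50 | 0.05 | 3.45 | 1.86 | 0.291 |
| 50 | 0.10 | 5.90 | 2.43 | 0.420 |
| 100 | 0.01 | 1.99 | 1.41 | 0.165 |
| 100 | 0.05 | 5.95 | 2.44 | 0.422 |
| 100 | 0.10 | 10.90 | 3.30 | 0.553 |

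**Step 2. Patient-level risk factors.** Ordinary logistic regression was simulated 400 times per scenario with no true effect of the factor. Assumed: 50 sites of 50 patients; intercept −1.1, an event risk of 1/(1 + e^1.1) ≈ 0.25 at an average site; site SD 0.6 on the logit scale, a latent ICC of 0.36/(0.36 + 3.29) ≈ 0.10. Two things were varied: the share of the factor's variance that lies between sites, and the correlation of its site mean with site risk.

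| Between-site share | Correlation with site risk | Mean log-odds per SD | Empirical SD / model SE | Type I error |
|---|---|---|---|---|
| 0% | 0 | −0.003 | 1.04 | 0.052 |
| 5% | 0 | 0.001 | 1.08 | 0.055 |
| 20% | 0 | 0.000 | 1.30 | 0.115 |
| 100% | 0 | −0.001 | 1.99 | 0.307 |
| 5% | 0.5 | 0.059 | 1.10 | 0.273 |
| 20% | 0.5 | 0.125 | 1.34 | 0.723 |

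With 400 runs, the simulation error of a rejection rate near 0.115 is √(0.115 × 0.885/400) ≈ 0.016.

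**Step 3. Plausibility check of the spurious effect.** The linear slope of site risk on the factor is √share × correlation × site SD. This gives √0.05 × 0.5 × 0.6 = 0.067 and √0.20 × 0.5 × 0.6 = 0.134. The simulated 0.059 and 0.125 are slightly smaller, as expected when a logistic model averages over unmodelled site variation.

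**Reading.** With no correlation with site risk, the coefficient is unbiased and only the standard error suffers, in proportion to the between-site share. With correlation, bias dominates: even a 5% share brings the error rate to 27%. Calendar period was not simulated; as an omitted variable it would act in the same way.

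**The case against.** The best defence is that a condensed article may leave model terms and variance estimators to a full analysis plan. The wording on regression carries no adjective such as ordinary, and a logistic model with centre terms would fit it. This stands in part. A reader might infer that the investigators decided to ignore clustering; the article does not support that. It is silent, and it excludes no such term. But the section is more than a pointer to a later plan: it fixes a normality cut-off, the comparison tests, the model families and the classes of explanatory variable. Hospital, country and period are absent from what it fixes.

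A second tempting inference is that all intervals and p-values will be too optimistic. The simulation contradicts this: with 0% to 5% of the variance between sites and no link to site risk, type I error is 5.2% to 5.5%.

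Third, the article promises no confidence interval for fatality or complication proportions, and as plain descriptions of the enrolled patients these need no between-site component. Step 1 therefore applies only if intervals are reported.

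Fourth, the ICC scales must not be mixed. A latent ICC of 0.10 corresponds to an observed-scale ICC of about 0.034 to 0.078 at event rates of 10% to 50%. At m = 50 that is a DEFF of 1 + 49 × 0.034 = 2.7 to 1 + 49 × 0.078 = 4.8, not 5.9.

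Finally, differences between sites in capacity or testing, and changes in treatment over the period, are plausible but not documented here. Only the scope for differing local diagnostic guidelines is on the page.

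**Conclusion.** The point holds in a limited form. As written, the tests and models take no account of hospital, country or admission period in a registry that is clustered by design and was extended well beyond its planned three months. Risk-factor associations can therefore be confounded by site and period. Uncertainty is understated for factors that vary between sites and for any interval placed on overall rates; it is about right for factors that vary almost wholly within sites.

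For patient-level factors confounding is the larger problem. The figures above illustrate its possible size and do not predict it for this registry: they rest on assumed site numbers, cluster sizes, ICC and correlation with site risk. The change should be made, because it protects the registry's main inferential output at little cost.

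**What to change.** In the Data Analysis section:

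1. Fit the logistic and linear outcome models with centre in the model. Use either centre fixed effects, or a random intercept for centre plus the centre mean of the key covariates. Pool small sites within country.
2. Add calendar period of admission as a covariate.
3. Use cluster-robust variance by centre for any confidence interval on fatality or complication proportions.

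Cluster-robust errors alone are not enough for the risk-factor models: they change the standard error and leave the confounded coefficient as it is. A random intercept without centre means removes the confounding only in part.

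The cost is a change of wording. The institution code is already recorded. Admission date is not listed by name in Table 1, but the length of stay that is listed there implies it, and its capture should be confirmed. The drawbacks are somewhat wider intervals, pooling of very small sites and, if centre fixed effects are chosen, no estimate for factors that are constant within a centre.

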## Data Collection

Information (variables) will be collected in the electronic database system RED Cap (Research Electronic Data Capture: https://www.project-redcap.org/). This database system will include 277 variables that will be distributed in 15 different files (Table 1).

**Table 1 T1:** Information to be collected.

Information	Variables

Demographics	*Age, gender, and other variables that will allow this population to be characterized*
Comorbidities	*Mainly cardiovascular pathologies including hypertension, coronary artery disease, heart failure and dyslipidemia, among others. Other high-risk comorbidities like cancer, immunosuppressive conditions, obesity, diabetes mellitus, COPD and renal failure will be included*.
Previous cardiovascular treatment	*ARB/ACEi/ARNI, and other drugs like beta blockers, diuretics, antiplatelet and anticoagulant agents*
Symptoms at admission	*Includes the most frequently reported (fever, cough, chest pain, and fatigue) and other less frequent variables (dysphagia, loss of taste or smell, myalgias, diarrhea…)*
Clinical findings at admission	*Basic hemodynamic and metric evaluation*
Cardiovascular complications during hospitalization	*Myocarditis, arrhythmias, heart failure, coronary artery events, venous or arterial thrombosis*
Laboratory test at admission	*Complete blood count, kidney and liver function tests, cardiovascular biomarkers and inflammatory biomarkers*
Electrocardiography	*Rhythm, QRS complex, bundle, branch block, corrected QT interval*
Chest X-Ray	*Pulmonary infiltrates, cardiomegaly, lung congestion, pleural effusion*
Echocardiography	*RV systolic function, pericardial effusion, cardiac tamponade, valvular function, vena cava dilatation, measurement of LV size and LV global systolic function*
Cardiovascular procedures performed during hospitalization	*Central catheters, use of inotropes, vasopressors or vasodilators, mechanical ventilation, ventricular assist devices (IABP, ECMO)*
COVID-19 treatment during hospitalization	*Steroids, antivirals, anti-inflammatory, anticoagulant or any other used treatment*
Laboratory tests at discharge	*Complete blood count, kidney and liver function tests, cardiovascular biomarkers and inflammatory biomarkers*
Outcomes during hospitalization and at discharge	*Length of stay, condition at discharge (alive or dead)*
Outcomes 30 days after discharge	*Rehospitalization, condition at follow up (alive or dead)*

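### On its natural reading, the plan fits linear regression to length of stay with deaths and live discharges pooled, so a factor's coefficient mixes mortality with recovery and can be attenuated or reversed

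*Protocol article*

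**What the plan says.** The Data Analysis section of the protocol article names two regression families for patient outcomes: "multivariate logistic or linear regression models, depending on the outcome variable to evaluate". It names no other.

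Table 1 (Data Collection) has two rows labelled as outcomes. The in-hospital row reads "Length of stay, condition at discharge (alive or dead", and the 30-day row reads "Rehospitalization, condition at follow up (alive or dead". Three of these four items are binary and go to logistic regression. Length of stay is the only quantitative one.

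A separate row, laboratory tests at discharge, is also quantitative ("Complete blood count, kidney and liver function tests, cardiovascular biomarkers and inflammatory biomarkers") but is not labelled as an outcome.

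The inclusion criteria require a hospital stay of more than 24 hours, with one exception: a patient who "dies during the first 24 hours after hospital admission" is also enrolled.

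The only time-to-event method is Kaplan-Meier, and it is tied to mortality: "survival analysis (the probability of death by time interval can be calculated) will be determined by the Kaplan Meier method". It is not applied to length of stay, and no competing-risk method is named.

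**The concern.** Live discharge and death both end a stay, but they mean opposite things. A linear model on pooled stays treats a death on day 1 as a very short stay, with nothing to mark it as a bad result. The inclusion rule sharpens this: apart from early deaths, every enrolled patient needs more than 24 hours of care, so stays under a day come from patients who died.

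The registry sets out to relate baseline characteristics, comorbidities and treatments to worse outcomes. The Introduction expects cardiovascular disease to go with mortality. For such factors the length-of-stay coefficient would depend on how many patients die and when, as well as on how long survivors take to recover. A lethal factor could then appear to have little effect on stay, or even to shorten it.

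**Working it through.** The article states no figure for length of stay, time to death or mortality, so there is nothing of its own to reproduce. All inputs below are assumptions.

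**Inputs.** Mortality is p0 = 0.15 without the factor and p1 = 0.30 with it. Times are lognormal with log-SD 0.7. Median time to live discharge is 10 days. Median time to death is 6, 10 or 14 days, the same with and without the factor.

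**Mean stays.** Mean = median × exp(0.7²/2) = median × 1.278.
- Live discharge: 10 × 1.278 = 12.78 days.
- Death: 7.67, 12.78 or 17.89 days.

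**Pooled difference.** With one binary factor, the linear coefficient is the difference in pooled means:

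D = (1 − p1) × (survivors' difference) + (p1 − p0) × (mean stay in deaths − mean stay in discharges without the factor).

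The second term is the distortion: 0.15 × (mean stay in deaths − 12.78).

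**Check for the 6-day case, no effect on survivors.** The pooled means are 0.85 × 12.78 + 0.15 × 7.67 = 12.01 and 0.70 × 12.78 + 0.30 × 7.67 = 11.24. The difference is -0.77.

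**Survivors' stay 15% longer.** The survivors' difference is 0.15 × 12.78 = 1.92 days, so the first term is 0.70 × 1.92 = 1.34.

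| Median time to death | Mean stay, deaths | D, survivors' difference 0 | D, survivors' difference +1.92 |
|---|---|---|---|
| 6 days | 7.67 | -0.77 | +0.57 |
| 10 days | 12.78 | 0 | +1.34 |
| 14 days | 17.89 | +0.77 | +2.11 |

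In the 6-day case about 70% of the survivors' difference is lost (0.57 of 1.92 remains). The sign reverses whenever that difference is below 0.77/0.70 = 1.1 days.

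**A second model.** Stay was simulated as the earlier of a latent discharge time and a death time, with 400,000 patients in each of 18 scenarios. Assumed values: discharge lognormal with median 9 days and log-SD 0.8; death hazard 0.01 or 0.02 per day; hazard ratio for death 2, 3 or 5; discharge time multiplied by 1.00, 1.25 or 1.67.
- No effect on discharge time (6 scenarios): the coefficient was negative in all 6, from -1.0 to -4.2 days.
- Discharge time also prolonged (12 scenarios): the coefficient was always below the latent difference (about 3.1 or 8.3 days). It was negative in 8 and positive in 4, with range -3.5 to +3.9 days.
- Survivors only, no effect on discharge time: the coefficient was still -0.9 to -3.3 days.

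The two models use different yardsticks. The first compares with the difference among survivors and the second with the difference in latent discharge time. In the second, death can only cut a stay short, so its distortion always runs downward.

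**The case against.** The strongest reply is that the article never says length of stay will be regressed. It appears once, as an item in a table of information to be collected, and not in the objectives or among the measures defined under Data Analysis. Other quantitative data exist, such as discharge laboratory values. An article may also leave the handling of deaths to a full protocol or analysis plan. This stands in part: the analysis is inferred. But the article does fix the choice of model family, and length of stay is the only quantitative variable it labels as an outcome. Followed as written, the text leads to the pooled linear model.

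A second reply is that hospital fatality, Kaplan-Meier curves and logistic regression of vital status would still reveal a lethal factor. That is right, and it limits the harm to the length-of-stay results.

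A reader might also infer that risk factors for early death *will* appear to shorten the stay. The documents do not support that. They give no times to death or discharge, and the working shows attenuation, no distortion or even the opposite direction under other inputs.

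A reader might further object that stay is skewed and that the normality check, with its fallback ("If the normality criterion is not met, a non-parametric test will be used"), is not applied to the regression. The article does not describe the distribution of stay, and linear regression does not need a normally distributed outcome variable. That argument should not be used.

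**Conclusion.** The point holds as a conditional one. If length of stay is modelled as the Data Analysis section implies, stays ended by death are pooled with live discharges, and the coefficient for any factor that affects mortality has no clear meaning. It *can* be attenuated or reversed. Under the stated assumptions and no effect on survivors' stay, the spurious difference runs from about -0.8 days (deaths earlier than discharges) through 0 (same timing) to +0.8 days (deaths later). Size and sign both rest on assumed mortality and times, none of which the article supplies.

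It would go too far to say that the bias works against a hypothesis of the registry. The Introduction expects a worse impact of the pandemic where cardiovascular disease is common, but states no hypothesis about length of stay. The fatality and Kaplan-Meier analyses are not touched by this point.

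**What to change.** State in the Data Analysis section that, if length of stay is modelled, the analysis is of time from admission to live discharge with in-hospital death as a competing event. Report cause-specific hazards for live discharge and for death side by side, with cumulative incidence curves or a Fine-Gray model. This replaces linear regression on pooled stays. Describe length of stay as median and interquartile range, separately for live discharges and deaths.

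Linear regression restricted to survivors is not an adequate substitute: in the second model it still gave a spurious difference when the factor had no effect on discharge time. A log transformation alone would not help either, since it leaves deaths and discharges pooled.

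The analysis needs only length of stay and vital status at discharge, both already in Table 1. The cost is slightly more analysis work and effects expressed as hazard ratios, which are harder to read than days.
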